### Control condition: time-matched control+TAU

To control for risk of bias from an undefined comparative treatment, and potential bias from dose effects, a time-matched TAU is included.^11 51^ In order to match the comparative brief intervention to usual practice within ARMS services, components of care were identified in an engagement meeting with ARMS service leads. These common core components could be described as supportive psychotherapy or ongoing care (needs-based emotional support, psychoeducation, normalisation and stress management) and were outlined as the interventions used by therapists as part of their normal clinical toolkit, alongside routine multidisciplinary care from the team. Patients work with different therapists who are ARMS clinicians and are not trained in MUSE. These clinicians will receive supervision on their practice through the routine supervision arrangements of their service and will record the interventions used within a per-participant TAU Therapist Pack (see online supplemental material 3). We will investigate how frequently and consistently these supportive psychotherapy interventions are offered to inform whether these interventions could act as a comparator intervention in future trials. This arm will be time-matched controlled, however, variation across services precluded using this comparator being defined as a controlled intervention. Number of sessions received in this group will be recorded for analysis.

10.1136/bmjopen-2023-076101.supp3Supplementary data

### Both groups: TAU

In addition to the trial allocated intervention (MUSE or TAU time-matched control supportive psychotherapy), both treatment groups will also receive additional usual care as clinically indicated. No treatments will be withheld on account of being part of the trial. This includes regular monitoring, signposting to appropriate local services for unmet needs, social support and crisis management when required from the multidisciplinary team. CBT is also a core intervention recommended by NICE Guidance and offered across ARMS services. However, in practice, it is not always offered to all service users. CBT may form part of the care in both conditions as part of usual care. We will investigate the number of CBT sessions received by participants in both groups and investigate whether MUSE impacts on the number of sessions required. Additional care will be based on clinical judgement and will be recorded for both arms of the study. These additional elements of care, including interventions and contacts that occur beyond the MUSE/time-matched period, will be analysed for variations and similarities in the care received between the two groups.

### Analysis

Analyses will follow intention to treat principles, with data analysed according to randomisation irrespective of treatment received. A full statistical analysis plan will be developed for the outcome measures and agreed with TSC before the end of data collection. Data will be reported in line with the Consolidated Standards of Reporting Trials^52^ (see figure 1).

**Figure 1 F1:**
[figure not shown]
Data to report in line with the Consolidated Standards of Reporting Trials.

### Sample size

As this is a feasibility trial there is no formal sample size calculation, interim analyses or stopping rule. The trial aims to recruit 88 participants with 70 participants completing the study (allowing for 20% attrition) to be able to robustly calculate the sample size for a definitive trial.^53^

### Statistical analysis

Feasibility outcomes will be analysed primarily: the ability of the trial to recruit participants, who reflect the diversity within the region and meet study inclusion criteria over the 9-month recruitment period, who complete assessment measures collected at baseline, postintervention and follow-up, until all participants complete the follow-up assessment or withdraw.

Descriptive statistics within each randomised group will be presented for baseline and follow-up points. All data will be summarised as appropriate using mean±SD and median±IQR for continuous outcome data; frequency and percentages for binary or categorical data; and rate for count data. Analysis will be via the latest version of R.

The signal of efficacy will be determined by examining the effect of each arm (MUSE vs supportive psychotherapy) on outcomes measures, estimated as change from baseline.

The effects will be estimated using generalised linear mixed effect models with the appropriate distribution and link function. Normal distributions with identity link will be used for continuous outcomes, and negative-binomial distributions with log link for count data outcomes. All binary or categorical outcomes will be analysed using generalised estimating equations (GEE). The mixed-effects models and GEE account for the repeated measurements per participant over the follow-up time points. All models will be adjusted for treatment arms and stratification variables. The mixed model approach taken will allow identifying the individual effect of the two interventions with relation to their baseline, as well as the difference in their effects through an interaction parameter of time and intervention. This can be considered as a model-based difference-in-difference analysis.

These models will be used mainly to estimate relevant parameters, since the trial is not powered for null hypothesis significance-testing. That is, while we are interested in identifying the magnitude of the signal of efficacy, we will not attempt to prove its significance.

In addition, a mediation analysis will examine how the different mechanism components mediate the estimated impact of the interventions on the primary outcomes, and a complier average causal effects analysis will determine the impact of the number of sessions on the MUSE effect.

If data are missing for a particular participant and outcome measure, this participant will be excluded from the analysis, for this outcome measure only, without further adjustment for missingness. However, the effect of missing data will be investigated additionally by sensitivity analysis using tabulation of rate of missingness across trial arms and imputation methods.

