### Trial eligibility criteria

#### Inclusion criteria

In contact with an ARMS service or accepted on an ARMS pathway by EIP services.Aged 14–35.Hallucinations/unusual sensory experiences scoring at least three on the Perceptual Abnormalities Subscale of the Comprehensive Assessment of ARMS (CAARMS).^6^
Hallucinations considered by the patient to be a key target problem.Judged to have been clinically stable for the preceding 2 weeks.

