### Randomisation and blinding

Eligible participants who have completed baseline assessments will be randomised and subsequent assessments will be scheduled from the point of randomisation. An independent web-based randomisation service (sealedenvelope.com) will be used for the trial. Randomisation will be in the ratio 1:1 to the two groups: MUSE+TAU (intervention) or TAU time-matched control (supportive psychotherapy+TAU (control). Randomisation will be stratified by site, gender (M/F/other) and age (14–17 years/18–35 years inclusive). Randomisation allocation will be independent and dynamically generated using a randomised modified minimisation method^31^ to assure allocation concealment along with preservation of allocation ratio. Randomisation allocation is made known to the CI and site PIs, the trial coordinator(s) and the trial therapists only at the point of randomisation, by email.

Research assessors for the trial will be blind to the allocation throughout the trial. Clinicians, therapists and participants will be unblind. Trial statisticians will be partially blind; In the first instance, for the analyses and reporting of main outcomes of the trial the Statisticians will be fully blind. However, for secondary sensitivity analysis such as impact of number of MUSE sessions on effect size) and the mechanisms investigations, the statisticians will be required to view which participants received MUSE treatment.

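### The efficacy signal is tied to each arm's change from baseline, and the between-arm estimate does not use the baseline outcome score

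*Protocol article*

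**What the plan says.** All of the analysis text is in the protocol's Statistical analysis section. The signal of efficacy is to be determined by "examining the effect of each arm (MUSE vs supportive psychotherapy) on outcomes measures, estimated as change from baseline". The mixed model is then said to identify the individual effect of each intervention relative to its own baseline, "as well as the difference in their effects through an interaction parameter of time and intervention". The section adds: "This can be considered as a model-based difference-in-difference analysis". On covariates it says: "All models will be adjusted for treatment arms and stratification variables". Randomisation and blinding gives the stratification variables as site, gender and age group. SOFAS and PSYRATS are measured at baseline, 12 weeks and 20 weeks (Table 1), but the baseline score is not listed as a covariate, and nothing is said about constraining the baseline means to be equal.

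Under Criteria for proceeding to a future trial, Go requires primary outcome data suggesting that the intervention may have an effect of clinical value. Refine and Stop are likewise worded in terms of an effect or no effect. None of the three names the contrast on which the effect is judged.

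Entry requires "Hallucinations/unusual sensory experiences scoring at least three on the Perceptual Abnormalities Subscale" of the CAARMS, together with "Hallucinations considered by the patient to be a key target problem" and two weeks of clinical stability.

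**The concern.** There are two separate issues.

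First, an arm's change from its own baseline is not an effect of the treatment in that arm. Participants are help-seeking and enter with symptoms above a threshold. Both arms receive usual care, which may include CBT, and the control arm also receives time-matched supportive sessions. The MUSE arm could improve with no specific effect of MUSE. Because the signal is worded as within-arm change and the Go rule names no contrast, a team could read that improvement as Go. The randomised control arm exists to prevent that reading.

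Second, the randomised contrast is planned as a difference-in-difference. With a free arm effect at baseline this is a comparison of change scores, which is less precise than an analysis that conditions on the baseline score. The section says the models serve mainly to estimate parameters and not to test, so interval width is what the between-arm analysis has to offer.

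**Working it through.** **Inputs from the protocol.** Target 88 recruited, 70 completing, 20% attrition (Sample size); 1:1 allocation (Randomisation and blinding), so about 35 completers per arm; assessments at baseline, 12 and 20 weeks; covariates arm, site, gender and age group.

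**Inputs assumed.** The correlation r between baseline and follow-up score is not given; I use 0.3 to 0.8. The outcome SD is not given, so results are in SD units. The SD is taken as equal at baseline and follow-up.

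**The plan's own figure.** 70/(1 − 0.20) = 87.5, rounded up to 88. It reproduces. The protocol states no precision for the efficacy contrast, so there is nothing further to reproduce.

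**Within-arm change with no treatment effect.** If participants average m SD above their population mean on the outcome at entry, expected change from regression to the mean alone is −(1 − r) × m. As an illustration, suppose selection were on the outcome itself, above its population mean. Then m = √(2/π) = 0.798.

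- r = 0.3: −0.7 × 0.798 = −0.56 SD
- r = 0.5: −0.5 × 0.798 = −0.40 SD
- r = 0.7: −0.3 × 0.798 = −0.24 SD

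A simulation gave the same within-arm values and a between-arm difference in change of 0.00 in each case. These figures show the mechanism and are not a forecast: actual entry is on CAARMS, not on SOFAS or PSYRATS, so the shift on those scales is unknown and probably smaller.

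**Precision of the between-arm difference at one visit.** Variance per participant, in units of the outcome variance:

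- change score, or difference-in-difference with a free baseline arm effect: 2(1 − r)
- baseline score as covariate, or common baseline mean: 1 − r²
- ratio: (1 − r²)/[2(1 − r)] = (1 + r)/2, so the reduction is 1 − (1 + r)/2 = (1 − r)/2

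The standard error is √(variance × 2/35). At r = 0.5 this is √(1.00 × 2/35) = 0.239 against √(0.75 × 2/35) = 0.207.

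| r | Difference-in-difference SE | Baseline-adjusted SE | Variance reduction |
|---|---|---|---|
| 0.3 | 0.283 | 0.228 | 35% |
| 0.5 | 0.239 | 0.207 | 25% |
| 0.7 | 0.185 | 0.171 | 15% |
| 0.8 | 0.151 | 0.143 | 10% |

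A generalised least squares calculation for all three time points (compound symmetry, 35 per arm), run at r = 0.3, 0.5 and 0.7, gave the same pairs. A free arm effect at baseline returns the change-score standard error, and a common baseline mean returns the baseline-adjusted one. At r = 0.5 the 70 completers do the work of 70 × 0.75 = 52.5 in a baseline-adjusted analysis.

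**Chance imbalance.** Given a baseline difference d between arms, the difference-in-difference is displaced by −(1 − r)d. With 44 per arm, d has SD √(2/44) = 0.213. A d of 0.3 SD, about 1.4 times that, displaces the estimate by 0.5 × 0.3 = 0.15 SD at r = 0.5. Over repeated randomisations this averages to zero.

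**The case against.** The strongest reply is that the plan is comparative. The Primary objective is the preliminary effect of MUSE plus usual care against the time-matched control, the sentence defining the signal itself sets one arm against the other, and the interaction is planned. A reader might infer that regression to the mean biases the trial's treatment estimate. It does not: it cancels in expectation in the interaction and affects only the within-arm reading. A reader might also infer that the plan makes natural improvement in the MUSE arm sufficient for Go. The rule does not say that. It leaves the contrast unnamed, and progression also depends on delivery, engagement, fidelity and safety criteria.

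It can also be said that the models are adjusted, for site, gender and age group; that the article gives no model equation, so the SAP, which is not among the documents, could constrain the baseline means and remove the loss; that a difference-in-difference is a valid estimator in a trial that disclaims testing; and that two weeks of stability at entry works against enrolling people at a peak.

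Most of this stands, and it limits the point. It does not answer two things: the text attaches the signal to change from baseline and gives the between-arm difference as an addition, and the analysis as described leaves unused a baseline score that is already collected. Naming a better use of data in hand is a comment on the method stated, not a complaint about missing SAP detail.

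**Conclusion.** The point holds as a recommended change, in two parts.

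The Statistical analysis section should not treat within-arm change as an intervention effect, and the progression rule should name the randomised contrast. The amount by which within-arm change would mislead cannot be derived from the document.

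The between-arm estimate is valid but less precise than the same data allow. The variance saving is 35% to 10% for r of 0.3 to 0.8. It rests on equal SDs at baseline and follow-up, about 35 completers per arm, and a free arm effect at baseline, which the covariate sentence implies without stating it as an equation. A reader might take the 25% at r = 0.5 as the loss in this trial. The protocol gives no correlation, so only the range can be supported.

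**What to change.** In the Statistical analysis section, and in the SAP that is to be agreed with the steering committee before data collection ends:

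- State that the signal of efficacy is the randomised between-arm difference in each primary measure at 12 and at 20 weeks, with its confidence interval.
- Estimate it with visit-specific arm effects, adjusting for site, gender and age group, and either enter the baseline score of that outcome as a covariate or keep baseline as an outcome row with its mean constrained equal across arms.
- Present within-arm change as descriptive, and drop the description of it as each intervention's individual effect.
- Under Criteria for proceeding to a future trial, say that Go, Refine and Stop are judged on this between-arm difference.

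The cost is wording and a small change to the model specification. Baseline assessments are completed before randomisation, so no extra data, visits or participants are needed.

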### Assessments

Assessors blinded to trial allocation will complete participant assessments at baseline, 12 weeks postrandomisation, and 20 weeks postrandomisation (see table 1). Sociodemographic information will be collected from the participant at baseline only (CSRI questions 1–3.5 as amended for the trial^32^).

**Table 1 T1:** Trial assessments and key participant procedures schedule

Assessments/procedures	Participant identification	Enrolment and baseline	Randomisation	Intervention weeks 1–12	12 weeks postrandomisation (±10 days)	20 weeks postrandomisation (±10 days)
Recruitment and eligibility discussions	X					
Informed consent		X				
CSRI Sociodemographic Q1-3.5		X				
Randomisation			X			
MUSE and TAU/TAU intervention				[figure not shown]		
Blinded assessments						
MUSE ARMS primary outcome measures: SOFAS and PSYRATS		X			X	X
CSRI service use Q4.1–4.4		X				
CSRI Q4.5 criminal justice services and Q5 medication		X			X	X
MUSE ARMS secondary outcome measures: CAARMS-PA, PHQ-9, GAD-7, ReQoL-20, ISI, ITQ/ITQ-CA, MMHQ		X			X	X
Subtype measures and cognitive tasks (1–2 subtypes selected per participant)		X			X	X
Treatment preference		X				
Unblinded assessments						
CSRI service use at follow-up Q4.1–4.4					X	X
Transition to psychosis data					X	X
Adverse event data					X	X
Therapeutic alliance STTS-R					X	
Participants interviews (withdrawals subsample)						
Participants interviews (MUSE completers sub-sample)						
Participants interviews (TAU subsample)						
Therapists interviews (subsample)						

ARMS, at-risk mental state; CAARMS-PA, Comprehensive Assessment of At-Risk Mental States subscale of Perceptual Abnormalities; CSRI, Client Services Receipt Inventory; GAD-7, Generalised Anxiety Disorder Assessment;; ISI, Insomnia Severity Index; ITQ/ITQ-CA, International Trauma Questionnaire/International Trauma Questionnaire - Child and Adolescent Version; MMHQ, Multi-Modal Hallucinations Scale; MUSE, managing unusual sensory experiences; PHQ-9, Patient Health Questionnaire; PSYRATS, Psychotic Symptom Rating Scales; ReQoL-20, Recovering Quality of Life; SOFAS, Social and Occupational Functional Assessment Scale; STTS-R, Satisfaction with Therapy and Therapist Scale-Revised.

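### Read literally, the missing-data rule turns the clinical-outcome models into completer analyses and discards observed visits that the planned mixed models could use

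*Protocol article*

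**What the plan says.** Assessors complete "participant assessments at baseline, 12 weeks postrandomisation, and 20 weeks postrandomisation" (Assessments). Under Statistical analysis, continuous and count outcomes go to mixed models and binary or categorical outcomes to GEE: "The mixed-effects models and GEE account for the repeated measurements per participant over the follow-up time points". The same section defines the quantity of interest, with the baseline score as the reference point: "The signal of efficacy will be determined by examining the effect of each arm (MUSE vs supportive psychotherapy) on outcomes measures, estimated as change from" that score. The difference between arms comes from a time-by-intervention interaction.

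The missing-data rule follows: "If data are missing for a particular participant and outcome measure, this participant will be excluded from the analysis, for this outcome measure only", and this is done "without further adjustment for missingness". Missingness is then explored by "sensitivity analysis using tabulation of rate of missingness across trial arms and imputation methods". The imputation method is not named.

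Two other statements bear on this. Under Analysis: "Analyses will follow intention to treat principles, with data analysed according to randomisation irrespective of treatment received". Under Sample size: "The trial aims to recruit 88 participants with 70 participants completing the study (allowing for 20% attrition").

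**The concern.** A mixed model fitted by likelihood needs no participant-level exclusion. It uses each visit that was observed, and it stays valid when drop-out depends on scores already recorded. The stated rule gives that up. Someone seen at baseline and week 12 but not at week 20 is lost from the whole model for that outcome, including its 12-week estimate. The main clinical estimate then describes completers, and in general it is safe only if data are missing completely at random.

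The plan tests no hypotheses on these outcomes, so the point estimates are the product. They feed the Go/Refine/Stop judgement (Criteria for proceeding to a future trial). Participants and therapists are unblinded (Randomisation and blinding), so drop-out that follows response differently in the two arms is plausible. The document does not show that it will happen.

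**Working it through.** **The plan's own figure.** 70 / (1 - 0.20) = 87.5, rounded up to 88. The target reproduces. 88 - 70 = 18 participants could be missing at week 20.

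**What deletion discards.** With 18 of 88 missing week 20, the rule leaves 70 participants. It drops 18 baseline records and between 0 and 18 observed 12-week visits, depending on when people leave.

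**Assumed inputs for the bias check (none is in the document).** Outcome SD 1, lower is better. Correlations are 0.5 (baseline with week 12), 0.5 (baseline with week 20) and 0.7 (week 12 with week 20). The true effect is -0.40 SD at both visits. In each arm 20% are lost after week 12. Drop-out in MUSE has log-odds rising with lack of improvement at week 12, by a slope per SD; control drop-out is random. Large simulated samples give the between-arm difference in change from baseline:

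| Slope | Deletion, week 20 | Deletion, week 12 | All observed visits, both weeks |
|---|---|---|---|
| 0.25 | -0.44 | -0.45 | -0.40 |
| 0.5 | -0.47 | -0.50 | -0.40 |
| 1.0 | -0.52 | -0.57 | -0.40 |
| 1.5 | -0.56 | -0.63 | -0.40 |

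The shift is therefore about 0.04 to 0.16 SD at week 20 and 0.05 to 0.23 SD at week 12.

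**Check at the trial's size.** 400 simulated trials of 88 were run with a random-intercept mixed model, correlation 0.6, slope 1.5 and a benefit of 0.40 SD (coded positive). Deletion gave 0.50 at week 20 and 0.58 at week 12. All observed visits gave 0.41 at both. The Monte Carlo SE is about 0.01.

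**Other drop-out patterns (table inputs, slope 1).**
- Same pattern and rate in both arms: each arm's change shifts by about -0.12 SD (week 20) and -0.17 SD (week 12). The shifts cancel, and the contrast stays at -0.40.
- Poor responders leave control only: the contrast moves towards zero, to -0.40 + 0.12 = -0.28 at week 20.
- Opposite patterns in the two arms: -0.40 - 2 × 0.12 = -0.64 at week 20.
- Same people leave MUSE before week 12, so only baseline is observed: the all-visits model gives about -0.53 at week 12 and -0.48 at week 20. Most of the bias remains.

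**Precision under random drop-out.** With 44 per arm, 44 × 0.80 = 35.2 complete. The variance of the change is 2 - 2 × 0.5 = 1.
- Deletion: SE at week 20 = √(2 × 1/35.2) = 0.238.
- All observed visits: regressing week 20 on baseline and week 12 leaves residual variance 0.48, so SE = √(2 × (0.48/35.2 + 0.52/44)) = 0.226.

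Simulation gave 0.239 and 0.228, a loss of about 5%.

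**SD.** At slope 1 the MUSE completers' SD is 0.99 at week 12 and 1.00 at week 20, against a true 1.0.

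**The case against.** The sentence could mean exclusion only when a participant has no usable data on a measure at all. The choice of repeated-measures models fits that reading. The text does not say so, however, and on that reading it still needs rewording.

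Several stronger conclusions are tempting, and the document does not support them.
- *The rule contradicts intention to treat.* The article explains its principle only as analysis by randomised arm whatever treatment was received. Excluding people for missing outcomes moves nobody between arms. The rule does fall short of keeping all randomised participants.
- *The efficacy contrast is biased whenever drop-out follows response.* It is not biased if the pattern is the same in both arms. Only the within-arm changes are.
- *The SD passed to the definitive trial is distorted.* In the scenario examined it barely moves.
- *The trial's primary analysis is compromised.* Feasibility outcomes are analysed first, no significance test is planned, and imputation is already a sensitivity analysis. The article gives no numerical threshold for Go/Refine/Stop, so no changed decision can be shown.

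It is also fair to say that the size of the bias depends on the scenario: at a slope of 0.25 it is at most 0.05 SD. A full analysis plan is still to be agreed with the steering committee. That does not dispose of the point, because the article already states a rule.

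**Conclusion.** The point holds as a should-fix. As worded, the rule makes the main clinical-outcome models completer analyses and wastes observed baseline and 12-week data, for up to about 18 of 88 participants. The planned imputation softens this but leaves the main estimate as it is.

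The harm falls first on each arm's change from baseline, which the article names as the signal of efficacy; this needs only response-related drop-out. Harm to the between-arm difference also needs drop-out that differs by arm, and its direction depends on which arm loses its poor responders. The tabulated range (-0.44 to -0.56 SD at week 20, -0.45 to -0.63 SD at week 12, true value -0.40) rests on the assumed correlations, 20% loss after week 12 and response-related loss in MUSE only. With random drop-out there is no bias, only the precision loss of about 5%.

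**What to change.** Replace the exclusion sentence with wording such as: *All randomised participants with at least one observed value contribute all their observed values, and mixed models are fitted by (restricted) maximum likelihood under missing at random.*

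For the outcomes assigned to GEE, keep GEE but use all observed visits, with multiple imputation or weighting based on the other visits, because plain GEE relies on data missing completely at random. Moving to a logistic mixed model is not needed, and it would change a marginal effect into a conditional one.

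Keep the completers analysis as a sensitivity analysis, and use imputation there to examine departures from missing at random. This second part matters because the new wording does not remove bias from people who leave before any follow-up visit for reasons linked to their unobserved response.

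If the authors meant exclusion only when a measure is wholly missing, the same wording settles it. The cost is one short paragraph. The mixed models and GEE are already planned and no further data are needed; the imputation or weighting is a modest extra analysis step.
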